### Who will take informed consent? {26a}, additional consent provisions for collection and use of participant data and biological specimens {26b}

The informed consent form will be created following the guidelines provided by the Ethics Committee of Iran University of Medical Sciences. The hospital’s secretary will be in charge of collecting the consent form from the patients, their parents, or caregivers. Before signing the consent form, all eligible patients or their parents will be fully informed about the interventions and possible adverse events. For more information regarding the consent form, please refer to Supplemental file 2.

### Interventions {11a}

The treatment session will commence 30 min after the first examination. Group A will first include the main treatment of CPT and then a placebo of aerobic exercise; group B will first include the main treatment of aerobic exercise and then a placebo of CPT (the inverse of Group A). The study will be conducted over 6 weeks, 3 times a week, with a total of 18 sessions. Make-up sessions will be allowed if a session is missed. The duration of the entire treatment session will last approximately 70 min.

### Group A (CPT and sham aerobic exercise)

At first, the participants will be placed in six standard postural drainage positions for a total of 30 min (Additional file 1: Supplemental Fig. 1A to F). Manual percussion and vibration will be performed on draining segments, in each position for 3–5 min. After completing the previous steps, the patient will be asked to sit down and cough for 1–2 min to expel the extracted secretions. In the following, in order to keep the patients blinded, the placebo aerobic exercise will be applied using a motorized stationary bike in two 15-min sections (Additional file 1: Supplemental Fig. 2). Between the two parts, 1–2 min will be allocated for rest. Throughout the exercise, the heart rate and percentage of arterial oxygen saturation (SpO2) of the patients will be monitored by a pulse oximeter. In this group, in order to eliminate the aerobic effects of the exercises, based on the method of previous studies [37], increasing the respiratory demands and breathing ventilation will be avoided until the end of the study. Therefore, the heart rate of the subject will not exceed 40% of HRmax during 30 min [38]. The total time of the exercises is 30 min, and at the end, 1–2 min will be given for coughing, if needed.

### Group B (aerobic exercise and sham CPT)

Progressive aerobic exercises will be conducted in two parts; the first will be 15 min on the treadmill and then a further 15 min on a stationary bike. Between the two sets, rest will be given for 1–2 min. A warm-up of 3 min with a gradual increase in speed will take place, and then 24 min of aerobic exercise with determined intensity (12 min on the treadmill and 12 min on a stationary bike), and finally a 3-min cool-down with a gradual decrease in speed will be conducted (Additional file 1: Supplemental Fig. 3A and B).

Throughout the training, the heart rate and SpO2 of patients will be monitored by a pulse oximeter. If there is a sharp drop in SpO2 below 85%, the heart rate is disproportionate to the conditions, and symptoms of severe shortness of breath or any other warning signs appear, the exercise will be stopped. During 24 min of aerobic exercises, the intensity of the exercise will be controlled through the heart rate of the patients (Table 2).

**Table 2 Tab2:**
[figure not shown]
Progression of exercise intensity

In order to keep patients blinded, Sham CPT will be done by the experienced conductor (NH) exactly like the main CPT in group A, considering draining areas and hand placements. Modifications are made to the postural drainage positions and the applied manual force. To perform postural drainage, in order to remove the effect of gravity, only 2 positions of supine and prone without inclination will be used; the treated areas and procedures will be similar to group A. In order to eliminate the effect of manual percussion, these strikes will be done very gently with pressure just like touching the skin. In order to eliminate the effects of vibration and pressure, hands will be placed on the desired areas and no vibration or pressure will be applied during exhalation. The total duration will last approximately 30 min. At the end, 1–2 min will be allocated for any coughing, if needed.

### Criteria for discontinuing or modifying allocated interventions {11b}

The medical recommendations of individuals, such as drug treatments and airway clearance methods, will not be changed. Due to the risk of cross-infection, two infected patients will not be in the same environment at the same time [3]. Participants are asked to use their 7% sodium chloride nebulizer at home before their treatment session, to prepare the airways [39].

### Strategies to improve adherence to interventions {11c}

To improve patient motivation, the comprehensive rehabilitation protocol will be offered completely free of charge, ensuring a seamless connection between the patients and their dedicated team of healthcare professionals including the physiotherapist (NH) and physicians. This regular contact will enable patients to promptly communicate any symptoms they may experience. Participants will be given gifts like toys, edibles, and accessories for more encouragement and cooperation. These gifts will be of equal value and given to the patients at the end of the treatment session, in packages. Also, the treatment room has been well designed in colors and music will be accompanied, to provide a better environment for children. In addition, patient adherence to home ACT, ACBT, will be checked at the beginning of every session and marked in a provided checklist. Participants will be called adherent if at least 90% of the prescribed ACT is successfully performed.

### Relevant concomitant care permitted or prohibited during the trial {11d}

Before the treatment starts, the ACBT technique, one of the main ACTs proven to be effective and safe [11], will be thoroughly taught to the patients and their parents and a guidance paper will be given to them. One week before the treatment starts, patients are asked to replace their sports activities with ACBT. Also, they are asked to do the technique on the days between their treatment days, twice a day, at home. The ACBT implementation is checked by the conductor every session. The steps to implement the technique are breathing control, chest expansion, and forced expiration technique (FET) [11].

### Provisions for post-trial care {30}

There is no anticipated harm and compensation for trial participation and post-trial care is not applicable.

### Outcomes {12}

All outcomes will be measured on two measurement time points: at baseline, and after 6 weeks.

#### Primary outcomes

Pulmonary function (FEV1): FEV1 will be assessed objectively using a spirometry test (Additional file 1: Supplemental Fig. 4). After recording a maximum of 8 trials, the maximum values recorded in liters and the predicted percentage will be reported as results. The minimal clinically important difference (MCID) for FEV1% in CF has been reported as 7.1% [36].

Functional capacity: 6MWT will be performed based on the recommendations of the ATS Association [40]. A 22.5-m corridor, in an enclosed space and flat surface, is marked by two cones. Patients will be asked to walk as fast as they can within 6 min and cover the greatest possible distance between the two points without running. In the end, the distance covered in 6 min will be measured as the test result. The MCID for this test in patients with CF has been calculated to be 33 m [36].

#### Key secondary outcome

Sputum culture: The test method will be based on the study of Marguet et al. [41]. Two respiratory mucus sampling methods are used according to the patient’s ability (expectorated sputum/swab method). The obtained samples will be sent to the laboratory within 2 h. The main and common pathogens of CF like *Pseudomonas aeruginosa*, *Staphylococcus aureus*, and *Burkholderia cepecia* are cultured on the samples [42]. The culture test will be positive if pathogen culture is observed in the sample. In addition, in cases where the culture test is positive, the microbe colony count is also done and its amount is reported qualitatively (low/medium/high).

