## Introduction

### Background and rationale {6a and 6b}

Cystic fibrosis (CF) is one of the most common autosomal recessive diseases [1]. Pulmonary complications of CF are one of the most common causes of death with 60% mortality, especially in children and adolescents [1, 2]. Despite the lower prevalence of this disease in the Asian continent (1 per 35,000 births), the number of patients has been increasing over the last two decades [1]. The CF affects various systems with more involvement in the respiratory system, causing very viscous, hard, and sticky mucous secretions that accumulate in the excretory pathways [1]. This is the basis for inflammation, recurrent infections, and tissue fibrosis [3, 4]. With every episode of pulmonary infection, a high percentage of a patient’s lung function is irreversibly lost [4]. As a result, the quality of life is reduced and can be very disruptive in daily activities [1–3, 5]. Therefore, choosing the appropriate treatment is important in treating these patients and reducing the disease burden [3, 6]. Airway clearance techniques (ACT) and physical exercise are introduced as one of the main components of treatment [1, 3, 7, 8].

Conventional chest physiotherapy (CPT) is the oldest form of ACT that was introduced in the 1940s [9] and is recommended as the standard treatment that can be performed by all people of all ages [10]. Based on the results of most studies, including guidelines and systematic reviews, there is no meaningful difference between different ACTs (including CPT, active cycle of breathing technique (ACBT), autogenic drainage (AD), and oscillating positive expiratory pressure (OPEP) devices). They all lead to more clearance of the produced sputum, reducing the recurrence of pulmonary infections and slowing down the progression of lung destruction. This in turn improves lung function and increases the quality of life for patients [3, 7, 8, 11–16]. Choosing the best method depends on the patient’s ability to perform, preference, and available facilities [7].

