Aerobic exercises are another important treatment option, as they increase endurance and cardiopulmonary fitness, aerobic capacity, mental health, and quality of life [17–19]. In addition, it is hypothesized that due to the increase in the respiratory rate and volumes and more passage of substances across the respiratory membranes and resultant increased ventilation, this treatment can also have significant effects on the evacuation of secretions [9, 20–23]. In addition to softening and moistening respiratory secretions, it also increases cough stimulation in patients and has been very effective in draining respiratory mucus [18, 20, 23, 24]. Limited studies also demonstrate its positive effects on respiratory infections [25, 26].

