### Objectives and hypotheses {7}

In this trial, we aim to include 30 children and adolescents of CF patients into a 1:1 randomized controlled trial study. We will compare the effects of conventional chest physiotherapy (CPT) and sham aerobic exercise in one group and aerobic exercise and sham CPT in the other group. The primary objective is to evaluate the effects of the 18-session aforementioned treatments on pulmonary function (FEV1) and functional capacity in children and adolescents with CF. The secondary objective is to assess the changes in sputum culture, pulmonary function (FVC), and quality of life of CF patients.

We hypothesize that there will be an increase by at least 7.1% in FEV1% percent predicted (minimally clinical important difference (MCID) considered for FEV1 [36]), a significant increase in the amount of FVC, at least 33-m increase in the distance covered in 6MWT (MCID considered for 6MWT [36]), a significant increase in the percentage of negative sputum culture tests and reduction of colony count tests after 6 weeks of aerobic exercise and CPT in CF patients, and a significant difference between the two groups. Also, the CFQ-R quality of life questionnaire score is expected to have a significant increase of at least 11.4 points in the physical domain, 7.3 points in the respiratory domain (MCIDs considered for CFQ-R [36]), and in the overall score.

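### The culture specimen (sputum or swab) follows the child's ability and is not held constant from baseline to week 6, so a change of specimen can look like a change in culture status, in either direction and possibly unequally by arm

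*Protocol article*

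**What the plan says.** The section Key secondary outcome, under Outcomes {12}, sets the specimen rule: "Two respiratory mucus sampling methods are used according to the patient’s ability (expectorated sputum/swab method". The result is then defined without regard to specimen: "The culture test will be positive if pathogen culture is observed in the sample". For positive cultures, "the microbe colony count is also done and its amount is reported qualitatively (low/medium/high", on one scale for both specimens.

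Outcomes {12} gives the timing: "All outcomes will be measured on two measurement time points: at baseline, and after 6 weeks". Objectives and hypotheses {7} says how the outcome is read. The trial expects "a significant increase in the percentage of negative sputum culture tests and reduction of colony count tests after 6 weeks" of each treatment, and also a difference between the groups.

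Background and rationale {6a and 6b} describes what the treatments do to sputum. Of airway clearance techniques, CPT among them, it says "They all lead to more clearance of the produced sputum". Of aerobic exercise it says "it also increases cough stimulation in patients and has been very effective in draining respiratory mucus".

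Eligibility criteria {10} admits ages 6 to 18 and does not require that the child can expectorate, so both specimen types are to be expected.

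**The concern.** The specimen is chosen by a characteristic that the treatments may alter. A rule based on ability, applied at two visits, allows one child to give sputum at baseline and a swab at week 6, or the reverse. The two results are then compared as if they came from the same test.

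If one specimen detects less than the other, the change of specimen alone can change the recorded culture status or colony grade. Randomisation does not protect against this, because the change happens after allocation. Blinding the assessor does not protect against it either, because the distortion lies in the specimen and not in how it is read.

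The arms also handle coughing differently. Under Group A, the child is asked to cough after the active CPT. Under Group B, coughing after sham CPT is left to need. Unequal switching between arms is therefore plausible.

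At stake is the outcome labelled key secondary, in a trial whose stated purpose is to prioritise one treatment if a significant difference appears. Equal switching in both arms would largely cancel between arms but would still distort the before-after change, which the hypotheses also cover.

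**Working it through.** The article gives no figure on this point to reproduce: no culture-positivity rate, no sensitivity for either specimen and no switching rate. The only input taken from it is 15 children per arm (Sample size {14}). Everything else below is an assumption, shown as a range.

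**Simple count.** Let k be the number of children in one arm who carry a pathogen, would be positive on sputum at both visits, and move from sputum to swab at week 6. Let r be the sensitivity of the swab relative to sputum. No pathogen clears.

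Expected spurious negatives = k × (1 − r). As a share of the arm, divide by 15.

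| k | r = 0.50 | r = 0.70 | r = 0.85 | r = 1 |
|---|---|---|---|---|
| 2 | 2 × 0.50 = 1.0 child, 6.7 points | 2 × 0.30 = 0.6, 4.0 points | 2 × 0.15 = 0.3, 2.0 points | 0 |
| 4 | 4 × 0.50 = 2.0 children, 13.3 points | 4 × 0.30 = 1.2, 8.0 points | 4 × 0.15 = 0.6, 4.0 points | 0 |

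One child is 1/15 = 6.7 points. These values are the between-arm distortion if no child switches in the other arm.

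**Reverse direction.** If the same k carriers are swabbed at baseline and give sputum at week 6, the swab is expected to find k × r of them and the sputum k. The spurious gain in positives is k − k × r = k × (1 − r). The table therefore applies with the sign reversed.

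**Check with carriage and imperfect sputum.** Let p be true carriage, s the share switching from sputum to swab, and Se the sensitivity of each specimen.

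P(negative at week 6) = 1 − p × [(1 − s) × Se(sputum) + s × Se(swab)]

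With all children on sputum at baseline, the spurious rise is p × s × [Se(sputum) − Se(swab)]. Assumed ranges are p 60–80%, Se(sputum) 95%, Se(swab) 50–90% and s 10–40%.

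- Smallest: 0.6 × 0.1 × (0.95 − 0.90) = 0.003, or 0.3 points (about 0.05 of 15 children).
- Largest: 0.8 × 0.4 × (0.95 − 0.50) = 0.144, or 14.4 points (about 2.2 of 15 children).
- Middle example, with p 80%, swab 70% and s 40%: baseline negative 1 − 0.8 × 0.95 = 24.0%; week 6 negative 1 − 0.8 × (0.6 × 0.95 + 0.4 × 0.70) = 32.0%; rise 8.0 points.

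If 10% switch in one arm and 40% in the other, the spurious between-arm difference is p × 0.30 × [Se(sputum) − Se(swab)]. This runs from 0.6 × 0.30 × 0.05 = 0.9 points to 0.8 × 0.30 × 0.45 = 10.8 points.

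**After the fix.** With the same specimen at both visits, s = 0 and the spurious change is 0 in every scenario. It is also 0 whenever the two sensitivities are equal.

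**The case against.** The strongest reply is that the article never says ability is judged again at week 6. In a population aged 6 to 18 it could be a stable trait: some children expectorate and the others are swabbed throughout. The culture method is also referred to a cited study, and the full protocol or a laboratory procedure may fix the specimen for each child. Neither is shown. This stands as a limit: the rule permits switching, and the article does not show that switching will happen.

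A reader might infer that children who respond to treatment will stop producing sputum, be swabbed and turn falsely negative. The documents do not support that as the main direction. The Background speaks of clearance, softened secretions and more cough, and nowhere says that children lose the ability to expectorate within 6 weeks. Easier expectoration would, if anything, move a child from swab to sputum and towards positive. Both directions are open.

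A reader might also infer that a material bias has been shown. It has not. No passage says that a swab detects less than sputum, and at equal yield the effect is exactly zero.

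It can also be said that a condensed article may leave specimen handling to other documents. That would answer a mere omission. Here the article does state a rule, and the rule makes the specimen depend on something that treatment may change.

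**Conclusion.** The point holds as a weakness in how the key secondary outcome is fixed. The specimen rule is not anchored to baseline, one positivity definition and one colony scale serve both specimens, and the treatments are expected to act on expectoration. A change of specimen can therefore pass for a change in culture status, in either direction and differently by arm.

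The size is unknown. It is zero if the specimens yield equally. It is roughly 2 to 13 percentage points of one arm's negative rate if 2 to 4 of 15 children, all carriers, switch in that arm and the swab finds 50–85% of what sputum finds. Those switching counts and sensitivities are assumptions.

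FEV1, the 6-min walk test and the sample size are not affected. The change should be made because it is cheap, and because without a record of specimen type the distortion can be neither detected nor examined afterwards.

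**What to change.** In Key secondary outcome, state that each child is sampled at week 6 with the same specimen type as at baseline. A child swabbed at baseline is swabbed at week 6 even if now productive. Record the specimen type at both visits. If a child who gave sputum at baseline cannot expectorate at week 6, take the swab and flag it. Enrolment has started according to Trial status, so recover the specimen type from laboratory records, where available, for children already sampled.

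Keep all randomised children in the main culture comparison and report specimen changes by arm. Add two sensitivity analyses: (a) same-specimen pairs only; (b) a negative week-6 swab after a positive baseline sputum counted as not converted. Same-specimen pairs should not be the main analysis. Restricting to them selects on an event after randomisation that treatment may influence, which would trade measurement bias for selection bias and shrink arms that are already small.

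The cost is one sentence in the sampling procedure, one form field and a little extra analysis. Both specimen methods are already in use. Some discordant pairs will remain, because a child who can no longer expectorate cannot be made to give sputum.

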### Trial design {8}

The current project is a double-blind 1:1 randomized controlled trial study designed to investigate and compare the effects of aerobic exercises and CPT in two parallel groups: group A consisting of CPT plus sham aerobic exercise and group B consisting of aerobic exercise and sham CPT. This study will be conducted at the CF specialized clinic of the Children’s Medical Center Hospital, Tehran, Iran; children and adolescents with confirmed diagnoses of CF will be randomly allocated to either group A or B.

Primary data points including FEV1, 6MWT, and secondary outcomes including sputum culture test (key secondary), FVC, and CFQ-R quality of life questionnaire will be assessed before and after treatments. It is expected that both treatments will have meaningful effects on the aforementioned variables and if significant changes are observed due to aerobic exercises compared to CPT, clinically, aerobic exercises will be recommended among treatment priorities.

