## Statistical methods

### Statistical methods for primary and secondary outcomes {20a}

Data will be analyzed using Stata version 16. The normal distribution of data will be analyzed by the Shapiro–Wilk test. If the distribution is normal, parametric tests will be used for analysis before and after the intervention. To determine the homogeneity of variances (i.e., variances approximately equal across groups), Levene’s test will be employed. If the variance is equal, the analysis of covariance (ANCOVA) will be used. The covariance variable in this test will be the initial data values before the intervention. The significance level of the tests is set at 0.05. In addition to the significance index, the effect size index is also used by Cohen’s *d* method to compare two treatment methods for each variable. Therefore, the effect of the intervention on each of the dependent variables is determined, regardless of the sample size. According to the new interpretation presented, the effect size can be divided and interpreted as follows: from 0.01 to 0.2, very small; from 0.2 to 0.5, small; from 0.5 to 0.8, moderate; from 0.8 to 1.2, large; from 1.2 to 2, very large; and more than 2, very large [46].

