### Methods for any additional analyses {20b}

Our study does not plan to conduct any additional analyses beyond the intended outcomes. The statistical methods used to analyze the outcomes are clearly mentioned in the text. If any additional or subgroup analysis of variables or confounding factors becomes necessary during the study, it will be justified in the final paper and reported in a section titled “Secondary data analysis.”

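### The key secondary outcome, sputum culture, is binary with a three-level grade in positives, but the only analysis stated is normality-based ANCOVA with Cohen's d

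*Protocol article*

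**What the plan says.** **Status.** Trial design {8} lists "secondary outcomes including sputum culture test (key secondary), FVC, and CFQ-R quality of life questionnaire".

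**Measurement.** The Key secondary outcome section under Outcomes {12} makes the result binary: "The culture test will be positive if pathogen culture is observed in the sample". It adds a grade for some children: "in cases where the culture test is positive, the microbe colony count is also done and its amount is reported qualitatively (low/medium/high". On specimens it says "Two respiratory mucus sampling methods are used according to the" ability of the child, by expectorated sputum or swab.

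**Hypotheses.** Objectives and hypotheses {7} expects "a significant increase in the percentage of negative sputum culture tests and reduction of colony count tests after 6 weeks". These are two separate statements, one on the share of negatives and one on colony count.

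**Analysis.** Section {20a}, headed for primary and secondary outcomes, starts with Shapiro-Wilk and allows parametric tests if the data are normal. After Levene's test it continues: "If the variance is equal, the analysis of covariance (ANCOVA) will be used", with the baseline value as covariate. Cohen's d is then used "to compare two treatment methods for each variable". No step is given for non-normal data, unequal variances, or binary or ordinal outcomes.

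**Completeness.** Section {20b} says: "The statistical methods used to analyze the outcomes are clearly mentioned in the text". Any analysis found necessary later is to be justified in the final paper and labelled as secondary data analysis.

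**The concern.** ANCOVA and Cohen's d compare means of a continuous variable. A yes/no result has no useful mean difference in standard-deviation units. A low/medium/high grade has an order but no distances. The outcome singled out as key secondary therefore has no usable prespecified analysis, and a test would have to be chosen after the data are seen.

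A second problem depends on how the colony hypothesis is tested. A grade exists only where the week-6 culture is positive. Being positive at week 6 is itself a result of treatment, so a comparison of grades among positives is not a comparison of randomised groups. If a treatment turns low-grade carriers negative, the remaining positives are the heavier carriers, and their average grade can rise although no child is worse.

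**Working it through.** **1. The plan's own figure.** Sample size {14} takes 11 per arm from an earlier trial and adds 30%: 11 × 1.3 = 14.3, rounded up to 15 per arm, 30 in total. This reproduces. The document gives no culture rates or grade distribution, so there is no figure for this outcome to reproduce, and the rates below are assumptions.

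**2. Does the stated route reach a method?** I applied Shapiro-Wilk to every possible data pattern.

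- 15 values, any 0/1 split: largest p = 0.00007.
- 15 values, all three grades present: largest p = 0.007, at 4 low, 7 medium, 4 high.
- 30 values: largest p = 2 × 10⁻⁷ (0/1) and 0.0001 (three grades).

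A split using only two of the three grades is equivalent to a 0/1 split, because the test does not depend on location or scale. At 15 values normality is therefore always rejected at 0.05, unless all values are identical, and {20a} then names nothing.

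One limit applies. If grades are tested in positives only, there may be fewer than 15 values. Repeating the enumeration for three grades gives a largest p of 0.036 at 10 values and 0.055 at 9. With nine or fewer positives some patterns pass, but only because the test then has little power. Passing would not make ANCOVA suitable for a grade.

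**3. Positives-only comparison, assumed example.** Each arm has 15 children, all positive at baseline: 5 low (1), 5 medium (2), 5 high (3). Arm A is unchanged. Arm B clears its 5 low-grade children and nothing else changes.

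- Arm A mean: (5×1 + 5×2 + 5×3)/15 = 30/15 = 2.0.
- Arm B, positives only: (5×2 + 5×3)/10 = 25/10 = 2.5. Share high: 5/10 = 50%, against 5/15 = 33% in A.
- Arm B, negatives as 0: 25/15 = 1.67. Negatives: 5/15 against 0/15.

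The same data favour A in positives only and B in all children.

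**4. Range of assumptions.** Start from equal thirds and let c₁, c₂, c₃ be the clearance of low, medium and high. The positives-only mean is Σ g(1−c_g) / Σ(1−c_g). The all-children mean is Σ g(1−c_g) / 3. The untreated value is 2.00 for both.

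- 60/30/10%: (0.4 + 1.4 + 2.7)/2.0 = 2.25; 4.5/3 = 1.50.
- 40/20/10%: (0.6 + 1.6 + 2.7)/2.3 = 2.13; 4.9/3 = 1.63.
- 20/20/20%: (0.8 + 1.6 + 2.4)/2.4 = 2.00; 4.8/3 = 1.60.

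The reversal appears only where clearance is concentrated in low grades.

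**5. A model without reversal.** Assume 20/25/30/25% negative/low/medium/high in one arm. Its positives-only mean is (0.25 + 0.60 + 0.75)/0.80 = 2.00. Multiply the cumulative odds by 4: 0.20/0.80 becomes 1.00 (50%), 0.45/0.55 becomes 3.27 (76.6%), and 0.75/0.25 becomes 12 (92.3%). The distribution is then 50.0/26.6/15.7/7.7% and the positives-only mean is (0.266 + 0.314 + 0.231)/0.50 = 1.62. At an odds ratio of 6 it is 1.55. Under a uniform shift, the positives-only comparison points the right way.

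**The case against.** **A condensed article may leave methods for categorical data to an SAP.** This holds for how a negative culture is coded in the colony comparison. It does not hold for the mismatch itself. Section {20a} is headed for secondary outcomes and assigns Cohen's d to each variable without condition, and {20b} declares the methods stated. One may say that ANCOVA is conditional on normality and so is never prescribed for culture. Then nothing is prescribed, which leaves the same gap.

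**The colony problem is not in the text.** This is largely right. A reader might infer that the plan compares grades in positives only and is therefore biased against the treatment that clears more infection. The documents do not support that. The outcome section says when the laboratory grades a sample; it does not exclude negatives from the analysis. The share of negatives is a separate hypothesis, so clearance would still be seen. Steps 4 and 5 show that a reversal needs a particular pattern of clearance.

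**Sampling.** A reader might also infer that a switch from swab to sputum will mimic or hide a treatment effect. Nothing says that a child's method changes between visits or goes unrecorded, and the test follows a cited study that is not at hand. Forcing the baseline method could leave a child who no longer expectorates without a valid week-6 sample. Recording the method is enough.

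**Severity.** FEV1 and the walk distance are continuous and are not touched by this point.

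**Conclusion.** The mismatch stands on the text alone: the key secondary outcome has no usable stated analysis. At 15 values the plan's own normality check fails for every yes/no split and for every split with all three grades present, and no next step exists. This needs no assumption about culture rates.

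The colony-grade point stands as a risk, not a certainty. In the assumed example the mean among positives moves from 2.0 to 2.5 while the all-children mean moves from 2.0 to 1.67. It requires that the comparison is made in positives only, which the documents leave open, and that clearance is commoner at low grades. With equal clearance the positives-only mean stays at 2.00, and under a common odds ratio it improves. The effect is confined to the colony-count comparison.

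**What to change.** For sputum culture only, remove Shapiro-Wilk, Levene, ANCOVA and Cohen's d, and state:

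- **Main analysis:** one four-level scale at week 6, negative < low < medium < high, in all randomised children. Use a proportional-odds model with baseline category as covariate, or a baseline-stratified Wilcoxon test if categories are sparse. Report the common odds ratio with 95% CI.
- **Percentage negative:** keep it as the separate hypothesis of {7}, reported per arm with exact CI.
- **Negatives:** say that a negative culture is the lowest category and not a missing grade, so that the multiple imputation in {20c} is not applied to it.
- **Sampling:** record sputum or swab at each visit and report any change by arm, without forcing the baseline method.

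The cost is a few sentences of analysis text and one field on the data form. The downside is low precision. With the assumed 20/25/30/25% distribution, an unadjusted Wilcoxon test has simulated power of about 0.51 at an odds ratio of 4 with 15 per arm, and 0.38 with 11. At an odds ratio of 2 with 15 per arm it is about 0.17. The proportional-odds model may not fit stably with four sparse levels, so the condition for moving to the rank test should be written down in advance.
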